#### Goal directed home program

This study will follow current best practice descriptions of Goal Directed Training and be delivered using the model home program approach outlined by Novak and Cusick [62]. See Table 2 for details of the intervention.

### Treatment fidelity

Two different types of intervention fidelity will be evaluated in this study. The first will assess clinician adherence to the active ingredients of each intervention protocol. Fidelity checklists containing the active ingredients of the respective intervention protocols have been developed to monitor treatment delivery against a priori criteria (see Additional file 1) [63]. Each criterion will be measured against a four point Likert scale. Adherence to the intervention approach will be determined by the computation of a percentage score [64].

Each intervention session will be video recorded. Assessment of intervention fidelity will include the random selection of 10% of the recorded intervention sessions, and observed by independent third-party reviewers trained in both intervention protocols. A fidelity rating of no less than 80% will be required to consider the intervention delivered to the intervention prototype (i.e. with fidelity).

The second fidelity measure is aimed at intervention receipt [63]. This will be monitored through completion of home practice logs. Participants will be provided with a log book to record practice sessions and note challenges and successes. In addition, parents will be asked to video record their occupational sessions for review, feedback and problem solving with respect to the active ingredients of the respective intervention protocols. These sessions will be reviewed with the treating therapist during home visits weekly. Parents will be asked to use readily available technology such as their mobile phone, if available, for the express purpose of feedback.

#### Ethical considerations

The study will be undertaken at Perth Children’s Hospital, the only dedicated children’s hospital in Western Australia. This study has been prepared in accordance with the principles and mandates set out in the Declaration of Helsinki 2008. Ethics approval has been obtained for this study through Perth Children’s Hospital Human Research Ethics Committees (HREC; ethics number 2014034). Parents and children will be provided with oral and written study information and have the opportunity to have their questions clarified before providing written assent/consent. Informed consent will be sought from primary caregivers and assent from child participants prior to commencement. Because children will be aged eight years and older their assent will be required for them to be enrolled in the study. Participation in this study is voluntary and family’s choices will be respected. Eligibility will be determined during the baseline assessment and randomisation will occur once eligibility has been determined. Children who receive botulinum toxin therapy will continue to receive this treatment, however their baseline assessments will be timed at least twelve weeks post their most recent Botulinum toxin-A injections and these treatments will be recorded.

#### Primary and secondary objectives

Our primary objective is to determine whether *Sense*© *for Kids* training, a somatosensory discrimination intervention, is more effective than placebo (Goal Directed Training via Home Programs) in improving somatosensory discrimination in children with HCP.

The specific hypotheses to be tested are:Children receiving six weeks of S*ense*© *for Kids* training will have higher scores on *sense*©*_assess* Kids [56] compared to children who received dose matched goal directed therapy via home program.Children receiving six weeks of S*ense*© *for Kids* training will demonstrate changes in fMRI activation of the somatosensory and related processing regions in response to tactile stimulation of the affected limb. Such changes will be greater than any activation changes seen in children who received dose matched goal directed therapy via home program.Children receiving six weeks of S*ense*© *for Kids* training will have altered structural connectivity (as assessed with diffusion MRI) of somatosensory processing centres.Children receiving six weeks of S*ense*© *for Kids* training will have higher scores on the Assisting Hand Assessment [57] compared to children who received dose matched goal directed therapy via home program.Children receiving six weeks of S*ense*© *for Kids* training will have comparable scores on the Goal Attainment Scale [58] and Canadian Occupational Performance Measure [59] compared to children who received dose matched goal directed therapy via home program.

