## Abstract

**Background:**

Of children with hemiplegic cerebral palsy, 75% have impaired somatosensory function, which contributes to learned non-use of the affected upper limb. Currently, motor learning approaches are used to improve upper-limb motor skills in these children, but few studies have examined the effect of any intervention to ameliorate somatosensory impairments. Recently, *Sense©* training was piloted with a paediatric sample, seven children with hemiplegic cerebral palsy, demonstrating statistically and clinically significant change in limb position sense, goal performance and bimanual hand-use. This paper describes a protocol for a Randomised Controlled Trial of S*ense© for Kids* training, hypothesising that its receipt will improve somatosensory discrimination ability more than placebo (dose-matched Goal Directed Therapy via Home Program). Secondary hypotheses include that it will alter brain activation in somatosensory processing regions, white-matter characteristics of the thalamocortical tracts and improve bimanual function, activity and participation more than Goal Directed Training via Home Program.

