**Discussion:**

This study will assess the efficacy of an intervention to increase somatosensory discrimination ability in children with cerebral palsy. It will explore clinically important questions about the efficacy of intervening in somatosensation impairment to improve bimanual motor function, compared with focusing on motor impairment directly, and whether focusing on motor impairment alone can affect somatosensory ability.

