#### Neuroimaging

##### Functional MRI

First level statistical analyses will contrast blocks (FEEL > REST) on an individual subject basis. Owing to the heterogeneous size and location of brain lesions seen within most cohorts, inter-subject registration (required for voxelwise statistics) may be difficult to perform reliably [98]. We plan to address this by performing region-of-interest analyses that measure the interhemispheric balance of activation between the sensorimotor cortices before and after therapy in the same child. S1, S2, and the dorsolateral prefrontal cortex (as delineated on single-participant templates) will be used. First-level results from all participants will be pooled into an analysis of variance (ANOVA), to investigate (A) changes by time-point, to search for an overall change in brain activation and (B) whether an interaction between time-point and treatment exists.

Task-related fMRI is considered an important neuroimaging modality in researching neuroplasticity. It is however recognised that task-related fMRI presents a “unique set of challenges” [99] that impact data analysis and interpretation. These challenges include but are not limited to: fMRI result variability, inability to distinguish the biological process that underlie changes in activation including alternative explanations such as compensatory activation or strategic shifts, the challenge in presenting task equivalency, and specific challenges in data analysis [99]. Many of these challenges of task-related fMRI are even greater in children with cerebral palsy in comparison to adult populations. As a group, the brain pathology and morphology of children with cerebral palsy is highly heterogeneous and often markedly abnormal owing to the wide range of aetiological processes and the early stage of development at which these processes occur. Additionally, clear relationships between brain structure and a child’s function have been challenging to establish [98]. These factors make standard functional neuroimaging analysis extremely challenging and at risk of limitation in the CP population [100]. Reid et al. make the case that multimodal imaging enables these unique challenges to be addressed and increases the robustness of functional neuroimaging research [99].

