##### Traditional diffusion MRI

Traditional diffusion MRI (dMRI) analysis methods make assumptions about brain structure-function relationships that may not hold in the context of significant brain pathology and cortical reorganisation, as occurs in children with CP [99]. To overcome this challenge, surface-based-fMRI guided tractography will be utilised, as previously demonstrated in children with CP [99], to extract thalamocortical tracts.

Mean FA will be taken for thalamocortical tracts at each time point and entered into an ANOVA to test for (A) the effects of time-point, to test for brain changes, and (B) a time-point – treatment interaction, to test whether treatments evoke different degrees of brain change.

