## Discussion

This study is a phase II comparative clinical trial [101], that builds on the findings of the recently completed phase I feasibility trial, reported by [name] et al. [47]. This comparative clinical trial will make a substantial contribution to our current knowledge base by exploring the efficacy of a somatosensory discrimination approach for children with CP, as well as observing changes in brain function and structure following a somatosensory intervention. This study will also be the first to compare a somatosensory intervention approach in children with HCP with a dose matched evidence based motor function focused intervention, in this case goal directed therapy via home program. It will provide valuable insights into treatment effectiveness and the underlying mechanism for change in the use of somatosensory discrimination training and will add to existing literature concerning the use of home programs. If children gain benefit from somatosensory discrimination training and increase their use of their affected hand and can transfer those skills to novel tasks, such as the children in our pilot work, this will improve functional independence and long-term outcomes for children with HCP. Understanding how a somatosensory approach may impact hand use, a child’s functional independence and self-efficacy will be an important contribution. Further to this, knowing whether a home program alone, without emphasis on sensory stimuli involved in any purposeful activity could have an incidental effect on somatosensory function, will also be an important finding. Results of this study will be disseminated widely through publications, international academic conferences and elsewhere as guided by our consumer representative.

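### Hypothesis 3 names no comparator, and the article credits some change over time to therapy, which two active arms without an untreated arm cannot support

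*Protocol article*

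**What the plan says.** **Hypotheses (Primary and secondary objectives).** Hypotheses 1, 4 and 5 are each set against the children who received goal directed therapy via home program. Hypothesis 2, on fMRI, adds a comparative sentence: "Such changes will be greater than any activation changes seen in children who received dose matched goal directed therapy via home program". Hypothesis 3 says only that children receiving the Sense for Kids "training will have altered structural connectivity (as assessed with diffusion MRI) of somatosensory processing centres". It gives neither a comparator nor a direction.

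**Abstract, Background.** The secondary hypotheses are summarised in one sentence ending "white-matter characteristics of the thalamocortical tracts and improve bimanual function, activity and participation more than Goal Directed Training via Home Program". That can be read as making the white-matter hypothesis comparative.

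**Planned imaging tests.** Under Traditional diffusion MRI, mean fractional anisotropy (FA) enters an ANOVA whose first test is "A) the effects of time-point, to test for brain changes". The second test brings in the randomised arm: "B) a time-point – treatment interaction, to test whether treatments evoke different degrees of brain change". Under Functional MRI, results from all participants are pooled to test "A) changes by time-point, to search for an overall change in brain activation", and then the interaction between time-point and treatment.

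**Attribution.** In the outcome section on functional MRI, the comparison of post- with pre-intervention activation is presented as a marker of neural change caused by therapy.

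**The home program on its own.** The abstract says the study will explore "whether focusing on motor impairment alone can affect somatosensory ability". The main Discussion counts "knowing whether a home program alone, without emphasis on sensory stimuli involved in any purposeful activity could have an incidental effect on somatosensory function" as an important finding.

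**Design.** There are two arms, both treated (Trial design). The Background gives the reason for an active control: withholding potentially effective treatment is considered unethical. Children are aged 6–15 and are assessed five times, with MRI at four of those visits, up to 12 months after the intervention (Study protocol). Under Functional outcome measures, a mixed model is to assess both within-group and between-group differences.

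**The concern.** Randomisation supports statements about the difference between the arms. It does not support statements about what either therapy did by itself, because no arm shows what would have happened without therapy. Three parts of the article go beyond that limit, or leave room to: hypothesis 3 as worded, the fMRI attribution sentence, and the statements about the home program alone.

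The rival explanations differ by outcome:

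- **Growth** applies to every outcome. The last scan falls a year after treatment ends, in children who may be as young as six at entry.
- **Retest learning** applies to the sensory tests, which are given five times.
- **Regression to the mean** also applies to the sensory tests. Eligibility requires impairment on sense_assess Kids and is determined during the baseline assessment, so the score that admits a child is also the starting point for measuring change.

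At stake is a secondary hypothesis, plus an advertised conclusion about the comparator, that could be declared supported when neither therapy had any effect.

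**Working it through.** **1. Which hypotheses name the control arm**

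| Hypothesis | Outcome | Control arm named? |
|---|---|---|
| 1 | sense_assess Kids | yes |
| 2 | fMRI activation | yes, in a second sentence |
| 3 | structural connectivity | no |
| 4 | Assisting Hand Assessment | yes |
| 5 | Goal Attainment Scaling, COPM | yes (comparable scores) |

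The abstract can be read as comparative for white matter, and the diffusion analysis already includes an interaction test. Hypothesis 3 is therefore out of step with both.

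**2. The article's own figure, used only to fix n**

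The inputs in Sample size are means 15.94 and 25.79 and SDs 9.72 and 11.93.

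- Pooled SD = √((9.72² + 11.93²)/2) = 10.881.
- d = (25.79 − 15.94)/10.881 = 9.85/10.881 = 0.9052, as stated.
- The two-sided t-test at 0.05 has power 0.797 with 20 per arm and 0.817 with 21 per arm, so 42 in total reproduces.

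The sample size is not in dispute. It supplies n = 21 per arm and 42 pooled.

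**3. How often would drift alone look like change?**

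The article gives no size for growth or retest effects and no test-retest correlation for change, so the following are assumptions:

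- there is no effect of either therapy;
- drift s is equal in both arms, at 0.2 to 0.4 SD of a single measurement;
- the correlation r between two visits is 0.5 to 0.8;
- two visits are compared, with a two-sided test at 0.05.

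The SD of a change score is √(2(1 − r)) in units of the single-visit SD. The standardised drift is therefore dz = s/√(2(1 − r)), and the one-sample t-test has noncentrality dz·√n. For s = 0.3 and r = 0.8, dz = 0.3/√0.4 = 0.474. The noncentrality is 0.474·√21 = 2.17 within one arm and 0.474·√42 = 3.07 pooled.

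| r | drift s | dz | within-arm, n = 21 | pooled time test, n = 42 |
|---|---|---|---|---|
| 0.5 | 0.2 | 0.200 | 14% | 24% |
| 0.5 | 0.3 | 0.300 | 26% | 48% |
| 0.5 | 0.4 | 0.400 | 42% | 72% |
| 0.8 | 0.2 | 0.316 | 28% | 52% |
| 0.8 | 0.3 | 0.474 | 54% | 85% |
| 0.8 | 0.4 | 0.632 | 79% | 98% |

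**4. The between-arm test under the same drift**

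The difference in mean change between arms is (drift + 0) − (drift + 0) = 0, so a common drift cancels. In a simulation of 40,000 trials with 21 per arm, the time-by-treatment test was significant in 4.95%, 4.93% and 5.01% of trials at drifts of 0, 0.2 and 0.5 SD of the change score.

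**The case against.** The strongest reply is that the randomised test for hypothesis 3 is already in the plan. The interaction is specified for both diffusion MRI and fMRI, and the abstract can be read as comparative. This stands: what is wrong is the wording of the hypothesis and its mismatch with the analysis, not a missing test.

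A reader might infer that the time-point tests are single-arm tests of treatment. The documents do not support that. The fMRI ANOVA pools all participants, and the time-point tests are described as looking for overall or brain change. The diffusion and fMRI analysis sections mention treatment only with the interaction. A reader might also infer that growth will be reported as a treatment effect. That is a risk left open by the wording, not a stated plan, and nothing makes the time-point test the decision rule for hypothesis 3.

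The statements about the home program are exploratory narrative. They are not among the five hypotheses and carry no confirmatory test. This lowers the weight of the point. It does not make the question answerable from change within the control arm.

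The rival explanations do not all reach hypothesis 3. Children are not selected on FA, and FA is not a task that improves with practice, so only growth clearly applies there. For the sensory tests the article has partial safeguards: several versions of the object recognition test, random ordering of wrist positions, and age norms. Practice before scanning is meant to limit familiarity effects in the fMRI task. None of these is tied to adjusting change over time.

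Finally, that a null result cannot distinguish two effective therapies from two ineffective ones is true of any superiority trial with an active control. The article justifies that choice, and it is not an error.

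**Conclusion.** The point holds in a limited form. Hypothesis 3 is the only hypothesis without a comparator and, read literally, is met by any change in the Sense arm. The fMRI attribution sentence and the statements about the home program alone claim or promise more than two active arms can show.

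The size is illustrative. Drift of 0.2–0.4 SD with correlation 0.5–0.8 gives 14–79% significant results within an arm and 24–98% in the pooled time test, with no therapy effect. Both inputs are assumed, and the result depends strongly on the correlation: at 0.3 SD, the within-arm figure falls from 54% to 26% as r goes from 0.8 to 0.5. The percentages should not be taken as estimates for FA in particular. The conclusion that the interaction stays near 5% needs only that the drift is the same in both arms.

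The primary objective and the planned between-arm conclusions are not affected.

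**What to change.** 1. Reword hypothesis 3 as a difference between arms in the change in structural connectivity, tested by the time-point by treatment interaction already planned for FA. This also brings it into line with the comparative reading of the abstract.
2. State that time-point main effects and within-group changes, for imaging and functional outcomes alike, are descriptive and will not be attributed to either therapy. Name growth as an alternative explanation throughout, and add retest learning and regression to the mean for the sensory tests.
3. Amend the sentence in the functional MRI outcome section so that pre-to-post change is described as change over time, with attribution to therapy reserved for the between-arm comparison.
4. Recast the statements in the abstract and the Discussion about motor-focused therapy or the home program alone as hypothesis-generating.

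The cost is wording only, with no extra arm, child or scan. The trial gives up a causal claim about each therapy on its own, which its design could not support.

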#### Study protocol

All outcomes will be measured within two weeks prior to commencement, again within two weeks following completion of intervention, then six weeks, six months and 12 months’ post intervention (± 2 weeks; Table 2). Assessment and intervention will take place in children’s homes or at school, whichever is the most convenient for families, except for MRI assessments which will take place at Perth Children’s Hospital. MRI data will be acquired at all time points, except the 6 weeks follow up.

Table 3 outlines when each outcome measure will be obtained. Time point one is the baseline assessment, time point 2 is at completion of 6 weeks of intervention, time point 3 is 6 weeks’ post intervention completion follow-up, time point 4 is 6 months post intervention completion follow-up and time point 5 is the 12 month post intervention completion follow-up.

**Table 3 Tab3:** Outcome measures

Outcome measure	Time Point					ICF Domain
	1	2	3	4	5	
Sense©_assess_*Kids*	•	•	•	•	•	Body structure/function
Magnetic Resonance Imaging	•	•		•	•	Brain structure/function
Assisting Hand Assessment	•	•	•	•	•	Activity
Goal Attainment Scaling	•	•	•	•	•	Activity and participation
Canadian Occupational Performance Measure	•	•	•	•	•	Activity and participation

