#### Functional outcome measures

A mixed-effects model with repeated measures will be used to assess within and between group differences. The corresponding baseline measure will be entered as a covariate in the model along with age and somatosensory capacity given these features were used in the randomisation process. The mixed model approach has the advantage of allowing for correlated data (repeated measures) and allows for missing observations within-subject. Model assumptions will be examined and if required transformations applied or non-parametric methods employed. Statistical significance will be set at 0.05.

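### The protocol predicts superiority on goal attainment and occupational performance in the abstract but comparability in its hypotheses, and its stated analysis cannot by itself establish comparability

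*Protocol article*

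**What the plan says.** The fifth hypothesis listed under Primary and secondary objectives concerns GAS and COPM. It predicts that children receiving Sense for Kids "training will have comparable scores on the Goal Attainment Scale [58] and Canadian Occupational Performance Measure [59] compared to children" receiving the dose-matched home program. The hypothesis just before it is worded differently: the same children "training will have higher scores on the Assisting Hand Assessment [57] compared to children who received dose matched goal directed therapy". The list therefore separates a superiority prediction for the Assisting Hand Assessment (AHA) from a comparability prediction for the two goal-based measures.

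The Background paragraph of the abstract sets out the secondary hypotheses in short form and says that the intervention will "improve bimanual function, activity and participation more than Goal Directed Training via Home Program".

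Table 3 (Study protocol) gives GAS and COPM the domain "Activity and participation". AHA is tagged as activity only, and no other outcome in the table carries participation.

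The section Functional outcome measures, under Statistical methods, gives one analysis: "A mixed-effects model with repeated measures will be used to assess within and between group differences". It adds "Statistical significance will be set at 0.05". The article states no equivalence or non-inferiority margin, no test of either kind and no confidence-interval rule.

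**The concern.** There are two linked problems.

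First, the same two outcomes are predicted to favour Sense for Kids in one place and to be similar between arms in another. With both statements on record, a significant difference in favour of Sense for Kids can be presented as confirming the abstract, and a null result can be presented as confirming the fifth hypothesis. A prediction that almost any result can support tests nothing.

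Second, a difference test controls the risk of declaring a difference that does not exist. It does not control the risk of declaring similarity when a relevant difference exists. Comparability needs a statement of how large a difference would still count as comparable, and an interval narrow enough to exclude anything larger.

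The comparator is described in the Background as evidence-based best practice, and GAS and COPM track the goals that the children choose. A claim that goal attainment was comparable would therefore be substantive, and readers would act on it.

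**Working it through.** **1. The hypotheses side by side**

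- AHA: superiority in the hypothesis list. The abstract agrees (bimanual function).
- GAS and COPM: comparability in the hypothesis list, superiority in the abstract (activity and participation).

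Could the abstract's phrase mean AHA alone? AHA is tagged as activity in Table 3, so the word activity could refer to it. But the abstract names bimanual function as a separate item, and participation in Table 3 belongs only to GAS and COPM. The conflict remains.

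**2. The plan's own sample size**

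Inputs (Sample size section): Wrist Position Sense Test means 15.94 and 25.79, SDs 9.72 and 11.93, two-tailed 0.05, power 0.8.

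- Pooled SD = √((9.72² + 11.93²)/2) = √118.40 = 10.88.
- d = (25.79 − 15.94)/10.88 = 0.905, as stated.
- Two-sample t-test power: 0.797 with 20 per arm, 0.817 with 21 per arm. So 21 per arm, 42 in total, as stated.
- Enrolling 50 allows for 1 − 42/50 = 16% attrition.

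The figure reproduces. It is sized to detect a difference of about 0.9 SD on another measure, not to show similarity on GAS or COPM.

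**3. Precision on GAS (illustration)**

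Assumptions: SD of 10, which the Activity section gives as the nominal SD of the T-score; an unadjusted two-sample comparison at one time point; 21 or 25 per arm.

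- SE = 10 × √(2/n): 3.09 for n = 21, 2.83 for n = 25.
- 95% half-width = t(0.975, 2n − 2) × SE: 2.021 × 3.09 = 6.2 points for n = 21; 2.011 × 2.83 = 5.7 points for n = 25.

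Suppose the true difference is 5 points (half an SD, an assumed value). The noncentrality is 0.5 × √(n/2), which is 1.62 for n = 21 and 1.77 for n = 25. The probability of a non-significant result is 0.647 and 0.590. For a true difference of 0.8 SD it is 0.284 and 0.209.

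**4. What a comparability test would need**

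The article gives no margin, so a range is shown in SD units, with true difference 0, 80% power and no covariate gain.

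- Equivalence (two one-sided tests at 0.05): n per arm = 2 × ((1.645 + 1.282)/m)².
- Non-inferiority (one-sided 0.025): n per arm = 2 × ((1.960 + 0.842)/m)².

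| Margin m | Equivalence, n per arm | Non-inferiority, n per arm |
|---|---|---|
| 0.3 SD | 191 | 175 |
| 0.5 SD | 69 | 63 |
| 0.8 SD | 27 | 25 |
| 1.0 SD | 18 | 16 |

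Simulated power of the equivalence test at 21 and 25 per arm is 4% and 10% for a 0.5 SD margin, 64% and 75% for 0.8 SD, and 88% and 94% for 1.0 SD.

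**5. Sensitivity to covariates**

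If the covariates correlate ρ with the outcome, the half-width shrinks by √(1 − ρ²). With ρ = 0.7 (assumed) the factor is 0.714, so 6.2 becomes about 4.5 points and 5.7 about 4.1. Equivalence power at a 0.5 SD margin rises to 44% and 58%.

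**The case against.** The strongest reply has four parts.

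- **Nothing says that a non-significant p-value will be read as comparable.** This is correct. A reader might infer it, because no other criterion is offered, but the article does not adopt that rule. The mixed model also yields an estimate and interval to which a margin could be applied.
- **A margin may sit in an analysis plan that is not shown.** That is possible, and the missing margin alone would not be a finding. It would not cure the conflict between the abstract and the hypothesis list, and the analysis that is stated is still mismatched with the hypothesis it is meant to serve.
- **Comparable need not mean two-sided equivalence.** Against an active best-practice control it could mean non-inferiority, or merely an expectation of similar gains. This stands: the word is undefined, and for that reason the table above shows both tests.
- **The numbers are assumption-bound.** This also stands. The SD of 10 is nominal, the half-SD difference is chosen for illustration, and the planned model adjusts for baseline, age and somatosensory capacity and uses repeated measures, so real intervals should be narrower. No SD is given for COPM, so nothing is computed for it. Narrower intervals still do not supply a criterion.

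Two further inferences should be resisted. A significant difference would not in itself refute comparability, since a small difference can be significant and still lie inside a margin. Nor does the plan leave these outcomes without any usable result, because an estimate with its interval can always be reported.

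**Conclusion.** The point holds on two counts. The article states incompatible hypotheses for GAS and COPM, and this follows from the text alone. It also pairs a comparability hypothesis with a difference test that cannot by itself establish it, and it offers no other criterion.

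The size is illustrative. Under the assumptions stated, the GAS interval is about ±6.2 to ±5.7 T-points, and a half-SD true difference would be missed about 65% to 59% of the time. A null result would then be weak evidence of similarity. How weak depends on the actual SD and the gain from adjustment, neither of which the article gives.

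Both measures are secondary. The primary objective, the sample size and the analysis of somatosensory discrimination do not depend on this hypothesis. It should be fixed, but it does not threaten the trial's main conclusion.

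**What to change.** State one hypothesis for GAS and COPM and use it in both the abstract and the list under Primary and secondary objectives.

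If comparability is kept, then before any unblinded outcome data are seen:

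- say whether it means equivalence or non-inferiority;
- give a justified margin for each scale;
- name the time point at which it is judged, since both measures are taken at five and none is singled out;
- judge it by the confidence interval of the adjusted group difference from the planned mixed model;
- state that a non-significant difference alone will not be read as comparable.

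If no margin can be justified, report the adjusted difference with its interval and drop the claim of comparability.

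The change is to wording only, with no new data or assessments. The cost is that comparability may not be demonstrable within a tight margin with 42 to 50 children, so the claim may have to be given up.
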